### Trial design

#### 1.1 Summary of trial design

The study will be a double blind clinical trial with random treatment allocation. Patients will be randomized into three parallel treatment arms. Treatment will consist of the application of topical 10% or 15% KOH in an aqueous solution for the two treatment groups, compared to a placebo-treated control group.

A total of five appointments are planned, one baseline and four follow-up visits. Screening will be done during the baseline visit to verify that all patients fulfill the inclusion and exclusion criteria, and have signed a written consent form, in addition to recording sociodemographic variables and a clinical history.

The efficacy of and tolerance to the treatment, as well as the appearance of new lesions, concomitant treatments and adverse affects will be evaluated in the follow-up visits.

During the baseline visit, the patient will be diagnosed and essential information will be recorded (inclusion/exclusion criteria, sociodemographic variables and clinical assessment). All valid/evaluable patients will be assigned a randomization code, up to a maximum of 60 patients who fulfill the inclusion/exclusion criteria. Neither the patient, their parents, nor the pediatrician will know to which group the patient has been assigned. Four follow-up visits are planned, at 15, 30, 45 and 60 days (± 3 days) from baseline. Each visit will include a clinical assessment, where the appearance of new lesions will be recorded. The efficacy of treatment and the tolerance of treated lesions since the last visit will be studied. A photograph of the affected area will be taken. If the patient misses the follow-up visit, compliance will be noted in the completion worksheet (which will be filled out in all remaining cases at 60-day follow-up). The randomization code will be revealed if the attending physician believes this to be appropriate. In this case the patient will be removed from the study, filling out the completion worksheet.

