#### 1.7 End of trial assessment

Each study participant can leave the study for two reasons:

1) Loss to follow-up (before the end of follow-up protocol, without successful treatment).

a. Lack of efficacy.

b. Choice of the patient.

c. Adverse effects.

d. Loss to follow-up (missing scheduled visits).

e. Breaking the blind.

f. Other.

2) Completion of follow-up.

g. Attended all scheduled visits

h. Success of treatment

A completion form should be filled out for all patients, whether they have finished the study or not.

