#### 1.8. Statistical methods and sample size

##### 1.8.1. Statistical analysis

The statistical analysis will be carried out on several different samples of the study population. The valid or valuable patient group is defined as those patients that fulfill all the inclusion criteria, none of the exclusion criteria, whose parents have provided consent for their participation and who have been assigned a treatment (randomized code). The safety sample is defined as the group of valid patients who have received treatment in the study at least once, whether or not its effectiveness has been assessed (who came to at least one follow-up visit). The intention to treat (ITT) sample is defined as the group of valid patients who have received treatment at least once and who have been assessed for its effectiveness at least once. The per protocol (PP) sample is defined as the group of patients that make up the ITT sample, have been assessed for efficacy and have not violated the protocol in any of the following ways:

- Violation of blinding.

- Greater than 10% missed treatments.

- Loss to follow-up by missing a scheduled visit.

The unit of analysis is the patient. Nevertheless, each patient can present multiple affected areas. An area is considered to be a set of lesions whose perimeter does not coincide with another affected area, with a single area being possible. No more than 15 affected areas per patient are expected.

A descriptive analysis of all the variables collected will be done, expressing quantitative variables as means, medians, minimums, maximums and standard deviations (SD), and categorical variables as frequencies and percentages.

The homogeneity of the study groups with respect to the following baseline parameters will be compared:

Demographic variables

Initial topography

Clinical history of associated diseases

History of treatments received (> 1 month)

To determine the existence of an association between a group and secondary efficacy variables at each period of follow-up, the single-factor ANOVA test will be used for quantitative variables (extent, number of lesions, etc.) and the chi-squared test will be used for categorical variables (cure).

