##### 1.8.2. Sample size calculation

The calculation of the sample size takes as its primary outcome treatment efficacy - the rate of complete elimination of MC at the final follow-up visit (60 days), as specified in a published clinical trial [7].

Based on this clinical trial, we expect a 20% cure rate in the control group and a 70% cure rate in one of the experimental treatment groups. To be able to detect these differences with a chi-squared test of two independent samples with a power of 80% at the 5% significance level, and with an estimated follow-up loss rate of 20%, there must be 20 patients per group.

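### The sample labelled ITT leaves out randomized children who were never treated or never assessed, and children who leave uncured have no day-60 assessment provided for

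*Protocol article*

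**What the plan says.** Section 1.8.1 first defines a valid group: eligible, consented and assigned a randomization code. It then defines the ITT sample more narrowly, as "valid patients who have received treatment at least once and who have been assessed for its effectiveness at least once". The per-protocol sample is a subset of this. It also excludes children with a blinding violation, more than 10% missed treatments, or a missed scheduled visit. The section plans ITT, per-protocol and safety analyses and names none as primary.

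Section 1.1 (Summary of trial design) sets follow-up visits at days 15, 30, 45 and 60, so efficacy is first assessed at about day 15. Section 1.3 sets the primary endpoint at day 60.

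Section 1.7 divides exits into two classes. The first is headed "Loss to follow-up (before the end of follow-up protocol, without successful treatment" and includes lack of efficacy, adverse effects and breaking of the blind. The second is completion, which includes success of treatment as well as attendance at all visits. When the code is broken, Section 1.1 adds: "In this case the patient will be removed from the study, filling out the completion worksheet".

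**The concern.** An intention-to-treat set keeps every randomized child in the assigned arm, so that the groups compared are those that randomization formed. The article already has that set (the valid group) but gives the ITT name to a smaller one. Two events after randomization decide membership: receiving an application and returning for an assessment. Since the per-protocol sample sits inside ITT, neither efficacy set keeps all randomized children.

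The exit classes add to this. A child who leaves uncured becomes a loss, while a child who is cured counts as having completed. The article provides no day-60 assessment for the first kind, although the primary endpoint is status at day 60. KOH is compared with saline, and the article itself foresees irritation and lists burning and pain as tolerance outcomes. Reasons for leaving may therefore differ by arm. With 20 children per group, a few exits can decide the result.

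**Working it through.** **Inputs from Section 1.8.2.** Cure rates: "we expect a 20% cure rate in the control group and a 70% cure rate in one of the experimental treatment groups". Test: "chi-squared test of two independent samples", "with a power of 80% at the 5% significance level". Size: "with an estimated follow-up loss rate of 20%, there must be 20 patients per group". Sidedness is not stated; two-sided is assumed.

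**Step 1: the plan's own figure.** With pooled variance and no continuity correction,

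n = [z(0.975)·√(2·p̄·(1−p̄)) + z(0.80)·√(p0(1−p0) + p1(1−p1))]² / (p1−p0)²,

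where p0 = 0.20, p1 = 0.70 and p̄ = 0.45:

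n = [1.960·√0.495 + 0.842·√0.37]² / 0.25 = 14.3, so 15 evaluable per arm. Then 15/0.8 = 18.75, so 19, against the stated 20. The figure reproduces to within one child. The inflation treats lost children as supplying no outcome: 20 × 0.8 = 16 per arm would be tested.

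**Step 2: what leaving out the exits does to the rates.** Assume that 70% and 20% are the rates among children assessed at day 60, that a fraction d of an arm exits uncured, and that exits count as not cured. The rate among all randomized is then p × (1 − d). The article gives only an overall loss of 20%, so the split by arm is an assumption. Leaving all exits out always shows 50 points.

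| Exits placebo / KOH | Placebo, all randomized | KOH, all randomized | Difference |
|---|---|---|---|
| 20% / 20% | 0.20 × 0.8 = 16% | 0.70 × 0.8 = 56% | 40 points |
| 0% / 20% | 20% | 56% | 36 points |
| 10% / 30% | 0.20 × 0.9 = 18% | 0.70 × 0.7 = 49% | 31 points |
| 30% / 10% | 0.20 × 0.7 = 14% | 0.70 × 0.9 = 63% | 49 points |
| 40% / 0% | 0.20 × 0.6 = 12% | 70% | 58 points |

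In the last row, leaving exits out understates the KOH effect.

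**Step 3: how few children matter.** Suppose four of 20 KOH children exit uncured and no placebo child does (uncorrected chi-squared):

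- 4/20 vs 9/16 assessed: p = 0.024. 4/20 vs 9/20 randomized: p = 0.091.
- 4/20 vs 11/16 assessed: p = 0.003. 4/20 vs 11/20 randomized: p = 0.022.

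At a result close to the planned 70%, the conclusion survives. At a weaker one, four children reverse it.

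**Step 4: power with all 20 per group kept.** By exact enumeration of the uncorrected chi-squared test at an unadjusted two-sided 5% level, power is 78.6% for 16% vs 56% and 67.1% for 20% vs 56%. The normal approximation gives 77.1% and 66.1%.

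**The case against.** Several stronger readings are tempting, and the article does not support them.

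- **That the main analysis is a completer analysis.** One assessment at any visit keeps a child in ITT, so a child seen at day 15 who leaves at day 20 remains. Attendance at every visit is a per-protocol condition, and no analysis is named as main. How a later exit's day-60 status is counted is not stated; a condensed article may leave that to the full protocol or analysis plan, so the silence is not itself an error.
- **That the result is biased in favour of KOH.** Adverse-effect exits on KOH would act that way. Lack-of-efficacy exits on placebo would act the other way, as the last row of the table shows. Section 1.2.3 has irritation stop the application and be reported at the next visit, so irritation alone does not end follow-up.
- **That the illustration measures the ITT definition.** It does not. The figures assume that the whole 20% loss is left out, whereas the definition alone removes only children never treated or never assessed.
- **That withdrawals are censored as uninformative in the time-to-cure analysis.** No censoring rule for them is given. The wording could even be read as carrying uncured children to the end of the study.
- **That the safety sample requires a follow-up visit.** The phrase "whether or not its effectiveness has been assessed (who came to at least one follow-up visit" is loosely worded, but the bracket most naturally explains what being assessed means. This is a matter of wording.

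What remains is stated text: the ITT definition itself, and exit rules under which children who leave uncured stop being followed. A missing-data rule placed elsewhere would not restore children whom the definition has already excluded.

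**Conclusion.** The point holds in a limited form. The set named ITT is a modified set with exclusions after randomization, and children who leave uncured do so with no day-60 assessment provided for. Either can distort the randomized comparison, in a direction that cannot be fixed in advance.

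If 20% exit, all exits are left out and all are uncured at day 60, a 50-point difference among those assessed corresponds to 40 points among all randomized with equal exits, or 36 if only KOH loses children. The split by arm is assumed. Section 1.7 establishes that these children were uncured when they left; that they remain so at day 60 is a conservative convention. The effect of the ITT definition alone cannot be sized, because the article gives no number for children never treated or never assessed.

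**What to change.** 1. Define ITT as all valid randomized children, analysed in their assigned arm, and name it as the set for the primary day-60 cure comparison.
2. Count a child who left under the first exit class of Section 1.7, and who has no day-60 status, as not cured. Keep a child who left under success of treatment as cured unless a later visit shows lesions. A rule scoring every child without a day-60 visit as a failure would misclassify these cures.
3. Report observed cases as a sensitivity analysis.
4. With the parents' agreement, seek the already scheduled day-60 assessment for children who stopped treatment or were unblinded. Reconcile this with the removal wording in Section 1.1.
5. If a full protocol or analysis plan exists, check it first for a missing-data rule and align the two.

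**Cost.** Items 1 to 3 change wording and analysis only. Item 4 changes a stated conduct rule and adds some visits. The figures become less favourable: at 20 per group and an unadjusted 5% level, power is about 79% for 16% vs 56% and about 67% for 20% vs 56%. By the Step 1 formula, 80% power would need 22 and 28 per group respectively. Any adjustment for two comparisons with placebo lowers power further.

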#### 1.3 Primary and secondary endpoints/outcome measures

Efficacy will be assessed in each of the areas detected in the previous visit. If there are new areas affected, they will be evaluated at the next visit (a description of the new lesion will be recorded in the topographic section of the patients record).

The principle efficacy variable (primary endpoint) will be calculated for each of the affected areas, as an indicator variable: (1. There is a lesion in the area/0. No lesion in the area) at 60 days from baseline. Each patient will be considered cured if they have no lesions in any of the treated areas.

Secondary efficacy variables (secondary endpoints) will be calculated for each location as follows:

- Number of lesions.

- Extent of area affected.

- Mean size of lesions.

○ < 0.5 cm.

○ 0.5 cm. - 1 cm.

○ > 1 cm.

- Efficacy of method: Ordinal scale with five categories.

○ Worsening (net increase in number of lesions or growth of existing ones).

○ No changes *(no modifications to the lesion).*

○ Slight improvement *(disappearance of up to 50% of lesions).*

○ Moderate improvement *(disappearance of more than 50% of lesions).*

○ Cure (*complete disappearance of lesions*) (primary endpoint).

- Digital photograph.

- Lesion density*: Number of lesions/Extent of affected area

*NOTE: If the parents locate new lesions between visits they should NOT treat them until the physician has clinically evaluated their topography*.

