In the case that the ANOVA cannot be used because a quantitative parameter does not fulfill the application criteria (non-normality/heteroscedasticity) the data will be transformed (logarithmic) from the original parameter, or a non-parametric analog test (Kruskal-Wallis) will be used. In all 2 × 2 comparisons (Group I, II vs. Placebo), the significance level will be adjusted for multiple comparisons.

The evolution of the quantitative efficacy parameters will also be assessed, by group, for the different time periods, using a repeated measures analysis.

The relationship between the baseline variables and the efficacy variables will be assessed at the end of the study, and in the case that an association is found, a multivariate analysis will be carried out to assess possible confounding factors of the group effect on adjusted efficacy: a multiple regression analysis will be used in the case of quantitative efficacy variables and a multinomial regression will be used in the case of qualitative variables.

The time from treatment to cure will be calculated as the difference between the date of first treatment and the disappearance of lesions or the end of the study (treatment initiation). Survival tables and the Kaplan-Meier statistic will be calculated to compare cure times between the different treatment groups. In the case that associations are found between efficacy variables and baseline conditions, a Cox proportional risk model will be adjusted.

Data analysis will be by ITT, by protocol and by safety sample.

In all cases a p-value below 0.05 will be considered significant.

Data will be analyzed using the statistical package "R": http://www.r-project.org.

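### Day-60 cure is compared by an unadjusted chi-squared test although the baseline number of affected areas is plausibly prognostic; fixing that one covariate in advance would be a cheap improvement of uncertain size

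*Protocol article*

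**What the plan says.** **Endpoint.** Section 1.3 of the protocol article scores each area for presence or absence of lesions at day 60 and then sets the patient-level rule: "Each patient will be considered cured if they have no lesions in any of the treated areas". Section 1.8.1 makes the patient the unit of analysis and adds that "No more than 15 affected areas per patient are expected", while noting that a child may have only one. Initial topography is among the baseline parameters to be compared between groups.

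**Test.** Section 1.8.1 says "the chi-squared test will be used for categorical variables (cure"). That sentence is introduced as covering secondary efficacy variables, with cure as its example. The tie to the primary outcome is in section 1.8.2: "To be able to detect these differences with a chi-squared test of two independent samples with a power of 80% at the 5% significance level".

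**Adjustment.** Section 1.8.1 provides a regression only where baseline variables are found at the end of the study to be related to efficacy. Its stated purpose is to look for confounding, and "a multinomial regression will be used in the case of qualitative variables". No covariate is named in advance for the primary comparison. Section 1.2.1 describes random allocation and mentions no stratification by disease burden. Section 1.8.1 also adjusts the significance level for the comparisons of the KOH groups with placebo, without naming the method.

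**The concern.** Under the all-areas-clear rule, a child with ten areas has ten ways to fail and a child with one area has one. Baseline burden is therefore plausibly prognostic by the construction of the endpoint, and it is known before treatment starts. An unadjusted test leaves that variation in the error term, and with about 16 evaluable children per arm a chance imbalance in burden can be sizeable.

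The conditional regression does not settle this. It is run only when the outcome data show an association, so the protocol leaves two possible answers to the primary question and lets the data decide whether the second one exists. What is at stake is some precision in the KOH-versus-placebo cure difference, and clarity about which result is primary.

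**Working it through.** **1. Inputs from section 1.8.2.** "we expect a 20% cure rate in the control group and a 70% cure rate in one of the experimental treatment groups"; "with a power of 80% at the 5% significance level"; 20% loss; 20 patients per group. The test is taken as two-sided.

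**2. The plan's own sample size.** With the mean rate (0.20 + 0.70)/2 = 0.45, the usual formula without continuity correction gives

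n = [1.96 × √(2 × 0.45 × 0.55) + 0.842 × √(0.20 × 0.80 + 0.70 × 0.30)]² / 0.50² = 14.3, so 15 evaluable per group.

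15/0.80 = 18.75, so 19. The stated 20 reproduces to within one patient. Twenty less 20% leaves 16 evaluable per arm.

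**3. Power of the planned test at 16 per arm (exact, uncorrected chi-squared).** 85.3% at the 5% level. At 2.5%, a Bonferroni reading of the multiplicity rule for two comparisons, it is 75.1%.

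**4. What the documents do not give.** They state neither the distribution of areas per child nor how strongly area count relates to cure. Both must be assumed, and the range shown.

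**5. Simulation.** The number of areas k is uniform on 1 to 15, 1 to 8 or 1 to 4. A child is cured with probability q^k, where q is the per-area clearance probability, solved so that average cure is 20% on placebo and 70% on KOH. For k from 1 to 15 with independent areas, q = 0.753 and 0.954. A placebo child with ten areas then has 0.753^10 = 6% chance of cure, against 75% with one area. For correlated clearance, a child-level normal effect with the stated SD is added on the logit of q. Each setting has 40,000 trials of 16 versus 16. The adjusted test is the t-test for arm in a linear model of the cure indicator on arm and log(k). Simulation error is about 0.2 point.

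| Areas within a child | k | 5%: chi-squared → adjusted | 2.5%: chi-squared → adjusted |
|---|---|---|---|
| independent | 1–15 | 85.5 → 90.8 | 75.2 → 85.0 |
| independent | 1–8 | 85.0 → 89.6 | 74.8 → 83.3 |
| independent | 1–4 | 85.3 → 88.1 | 75.2 → 81.1 |
| correlated, SD 1.5 | 1–15 | 85.3 → 87.3 | 74.9 → 80.1 |
| correlated, SD 1.5 | 1–4 | 85.6 → 86.1 | 75.2 → 78.3 |
| correlated, SD 3 | 1–15 | 85.2 → 85.4 | 75.2 → 77.4 |
| correlated, SD 3 | 1–4 | 85.6 → 85.2 | 75.5 → 76.9 |
| burden unrelated to cure | – | 85.2 → 84.1 | no change |

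The gain is about 3 to 6 points (5%) and 6 to 10 points (2.5%) with independent areas, and about 0 to 2 and 1.5 to 5 with correlated areas. About 1 point of the gain at 2.5% reflects the discreteness of the chi-squared test, which rejects 2.2% of null trials at that level (45% cure in both arms).

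**6. Type I error.** The adjusted linear test rejected in about 5% of null trials (4.8–5.3% across runs). A plain logistic likelihood-ratio test rejected in 7.6–7.7% when cure was 20% in both arms, so it is not a safe substitute at this size.

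**7. How often the conditional adjustment would run.** The protocol gives no criterion for an association. Taking a pooled p < 0.05 between areas and cure as the trigger, it fires in 53% of trials with independent areas on 1–15, and in 21% when cure probability is q^(√k), a correlated-area form.

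**The case against.** The strongest case against the point is that nothing here is an error. Randomisation makes the unadjusted chi-squared test valid, and chance imbalance is already part of its error rate. The stated target of 80% power at 5% is met without adjustment. The fall to about 75% arises only under a Bonferroni reading of the multiplicity rule, which is a multiplicity and sample-size matter and not a covariate matter. All of that stands.

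The power gain also leans on independent clearance. Areas on one child share one host and one bottle applied by the same parents (section 1.2.3), so correlated clearance is at least as plausible, and the gain is then small. Nor is area count a perfect measure of burden: an area is a set of lesions of any number, and section 1.3 lets new areas enter after baseline. This also stands, and it is why the gain must be given as a range that starts near zero.

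Two further objections stand in part. The plan does compare topography between groups and does provide adjustment, so one cannot say that adjustment is absent. But that adjustment is triggered by the data and often would not run. And a reader might call the multinomial model wrong for a yes/no outcome. The documents do not support that: section 1.3 also has a five-category efficacy scale, and with two categories a multinomial model is logistic regression.

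Choice of a covariate can be left to an analysis plan that is not shown. What keeps the point alive is that the protocol does state a choice: an unadjusted test, with adjustment conditional on the outcome.

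**Conclusion.** The point holds as a cheap precision improvement, not as an error in the plan. The only unconditional test tied to day-60 cure ignores a baseline value that is already recorded and plausibly prognostic, and the only adjusted analysis depends on the outcome data.

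A reader might infer that the plan gives up a definite 5 to 10 points of power. The documents do not support that. A gain of that order needs near-independent clearance of areas, or a strong link between area count and cure. A reader might also infer that the test is invalid or the trial underpowered at its stated level; neither follows, since power is about 85% at 5%. All of these figures assume 16 evaluable children per arm and the plan's own 20% and 70% cure rates.

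**What to change.** In section 1.8.1, name the primary comparison explicitly: day-60 cure, each KOH arm versus placebo, reported as a risk difference with its confidence interval from a linear model of cure on arm and log(number of affected areas at baseline). State that this single covariate is used whatever the baseline comparison or the outcome data show. Keep the unadjusted chi-squared test as a sensitivity analysis, and describe the association-triggered regressions as exploratory.

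The cost is wording only: no new data, visits or patients. The statistical price is one degree of freedom, and up to about 1 point of power at the 5% level if burden proves unrelated to cure.
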